### 2.2. Study Design

The VedieS study is an explorative, cross-sectional study. Two quantitative online surveys on a vegan diet and the intake of DS during pregnancy, infancy and early childhood (up to the age of 5 years) are carried out: The first survey focuses on vegans (parents and pregnant women) and the second survey on medical experts (pediatricians, gynecologists, general practitioners, pharmacists, dieticians). Each survey will take approximately 20–25 min to answer.

Recruitment for the survey is scheduled to take place between October 2023 and the end of July 2025. There is no survey restriction to Austria. Participants from Germany, Switzerland and Italy/South Tyrol, Liechtenstein, and Luxembourg (or other EU countries) can also answer the questionnaires and will be included in the evaluations. Since the survey is conducted in German, the survey refers to participants who understand the German language.

### 2.3. Participants

Vegans are recruited by public announcements, newsletters and social media (Facebook, Instagram) of cooperating specialized organizations and medical experts that forward survey announcements, posters, and flyers, as well as info sheets, to potential participants.

Participants will be forwarded an online link/URL to the anonymous questionnaire. Before they can start the survey, the topic and further details of the survey are explained in an introduction. Potential participants interested in the study will have the immediate possibility to participate in the online survey wherever they are.

Medical experts (pediatricians, gynecologists, general practitioners, pharmacists, dieticians) are recruited by being contacted via email and through the support of professional organizations, info sheets, notices in hospitals, medical offices, pharmacies, and universities. Participants interested in the study will have the immediate possibility to participate in the (online) survey via an (online) link/URL.

The questions asked within the questionnaire determine whether participants are eligible for the survey or are excluded (inclusion/exclusion criteria).

More than 15 organizations forward/forwarded the survey via their newsletter and/or social media.

### 2.4. Eligibility Criteria

Inclusion criteria for vegans:1.Females/diverse participants (ages 18 and over) who follow/followed a vegan diet during their pregnancy/pregnancies (if there is/was more than one pregnancy, at least during one of their pregnancies).2.Parents (female/male/diverse—ages 18 and over) who feed/fed their child/children (if there is more than one child, at least one of them) a vegan diet at least between the ages of 0 and 5 years.3.Vegan mothers/diverse participants (ages 18 and over) who breastfeed/breastfed their infant(s)/child(ren). Answering questions regarding their infant(s)/child(ren) up to the age of 5 years will be included.4.Pregnant and breastfeeding women/gender diverse participants/parents (f/m/d) who make rare exceptions to their vegan diet and a vegan diet of their child(ren)—up to the age of 5 years. Inclusion in the survey depends on the frequency of exceptions → determined through questions/given answers within the survey. Participants that consume animal products a maximum of twice a month will be included; hence, participants who do not make vegetarian, pescetarian, or omnivorous exceptions more than twice a month will be included.5.Confirmation of the participant information (online—addressing the subjects, purpose and process of the study, opportunities for discussion of further questions, duration of the questionnaire, who is conducting the study, possibility for further inquiries).

Exclusion criteria for vegans:1.Females/diverse participants who change/changed their vegan diet (eat/ate a vegetarian or omnivorous diet) during their pregnancy/pregnancies.2.Parents who do not feed/have never fed their children a vegan diet at least up to the age of 5 years (if vegan mothers followed a vegan diet during their pregnancy, exclusion only relates to questions concerning their children).3.No confirmation of the participant information (online).

For inclusion in the study, at least one inclusion criterion (plus participant information) must be fulfilled. Exclusion (or not inclusion) will happen if only exclusion 3 is fulfilled. If only 1 or 2 is fulfilled, and 3 is not, participants will be included in the survey.

Inclusion criteria for medical experts:1.Gynecologists, pediatricians, general practitioners, pharmacists, and dieticians with or without a consulting focus on vegans.2.Confirmation of the participant information (online).

Exclusion criteria for medical experts:1.Other medical specialists not mentioned in the inclusion criteria.2.No confirmation of the participant information.

For inclusion in the study, all criteria must be fulfilled. Exclusion (or non-inclusion) will happen if only one exclusion criterion is fulfilled.

All participants have to understand the German language in order to answer the questionnaire.

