#### 2.1.1. Primary Objectives

##### Determination of Main Influential Factors That Affect Vegans Regarding Their Diet During Pregnancy and When Feeding Their Children (Up to the Age of 5 Years)

Influence by medical experts or other influences (e.g., social environment, Internet and social media, magazines) concerning the decision for or against a vegan diet should be clarified. Depending on the source of information, the possible risks of a vegan diet during pregnancy, infancy and early childhood can be misjudged.

The identification of information sources for vegans on dietary supplements, as a reason for the approval or rejection of DS (during pregnancy, infancy and early childhood), embodies trustworthiness by ranking.

It should be determined which information on DS (during pregnancy, infancy and early childhood) is used and whether this information appears trustworthy or causes uncertainty. Information received affects selection, intake, or avoidance of certain DS. The health impact of selected sources of information on DS can be made visible. Medical expert advice and other opinion-forming aspects (e.g., social environment, Internet and social media, magazines) should be ranked according to their relevance. Main sources of information should be identified.

This can be an important approach for the improvement of information supply on DS in a vegan diet and for minimizing risks preventively. By recognizing sources of information classified as the most important for vegans, the main causes of frequent inadequacies in the provision of information could be identified and if necessary, positively changed.

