### 2.7. Statistical Methods and Data Analysis

The survey data will first be exported from LimeSurvey to Excel (Microsoft Corp., Redmond, WA, USA) and then analyzed using IBM SPSS Statistics version 31 (IBM Corp., Armonk, NY, USA) and R version 4.5.1 (R Core Team). Descriptive statistics will be used to summarize the results. For example, averages and standard deviations will be calculated for numeric variables, while frequencies and percentages will be reported for categorical data. Diagrams such as bar charts and boxplots will visualize the results. Depending on the type of data, different methods will be used to compare groups. Categorical variables will be analyzed using chi-square tests, and continuous variables with ANOVA. For yes/no outcomes (such as whether participants use DS or whether medical experts recommend them) logistic regression models will be applied to examine possible influencing factors. We plan to use both simple (univariate) and more complex (multivariate) logistic regression models. In the multivariate models, we will include relevant background characteristics like age, gender, education, household situation, or medical profession to better account for possible confounding effects. Since the study is exploratory, *p*-values will be reported descriptively. There will be no correction for multiple testing. Comparisons between groups will be carried out only when there is a sound theoretical reason and enough data to support it.

Possible comparisons within the vegan participant group include

-People living in rural vs. urban areas;-Supplement users vs. non-users (for themselves or their children);-Participants who changed their diet during pregnancy vs. those who did not;-Individuals who received professional advice vs. those who used informal sources like social media.

Possible comparisons within the group of medical experts include

-Those who support vs. those who reject vegan diets during pregnancy and childhood;-Those who advise supplementation vs. those who discourage it;-Differences between professions (e.g., pediatricians, pharmacists, dietitians).

Depending on the final data, additional group comparisons will be added. We will only report comparisons that are well justified and provide useful insights.

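### The vegan eligibility rules contradict each other and the planned changed-versus-unchanged comparison, and entry under-represents people who gave up the diet, so the frequencies of change and of its causes are understated

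*Protocol article*

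**What the plan says.** **Entry.** Section 2.4 of the protocol article requires that "at least one inclusion criterion (plus participant information) must be fulfilled". Criteria 1 to 4 cover a vegan diet in pregnancy, a vegan-fed child, vegan mothers who breastfeed, and people in these groups who make rare exceptions. The pregnancy criterion admits those who "follow/followed a vegan diet during their pregnancy/pregnancies (if there is/was more than one pregnancy, at least during one of their pregnancies".

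**Exclusions.** Exclusion 1 is "participants who change/changed their vegan diet (eat/ate a vegetarian or omnivorous diet) during their pregnancy/pregnancies". Exclusion 2 concerns parents who did not feed a child vegan; for mothers who were vegan in pregnancy, it removes only the child questions. Exclusion 3 is failure to confirm the participant information.

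**Rule for combining them.** The same section continues: "Exclusion (or not inclusion) will happen if only exclusion 3 is fulfilled", and "If only 1 or 2 is fulfilled, and 3 is not, participants will be included in the survey".

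**Analysis and aims.** Section 2.7 lists as a possible comparison "Participants who changed their diet during pregnancy vs. those who did not". A primary objective in section 2.1.1 is that influence "concerning the decision for or against a vegan diet should be clarified". Section 3.1 bases all findings on how frequent and prevalent the responses are. Section 3.2 lists maintenance of the diet, and the reasons for altering it, among the secondary outcomes.

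**The concern.** A person who changed diet during pregnancy is excluded by one sentence, included by a later one, and needed as a comparison group in section 2.7. Whoever codes the dataset must choose between these rules, and the choice decides whether the comparison exists.

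The combining rule does not settle everything. Someone who gave up the diet and meets no inclusion criterion still cannot enter. Section 2.6.1 itself assumes that some vegans change diet in these life stages because of nutrient worries, limited counselling or external pressure, and the Introduction hypothesises that critical advice could lead to dietary change. Entry is thus selected on a behaviour that a primary objective seeks to explain. Percentages are the main output of the study, and they are what this selection distorts. The limitations in section 5.2 cover self-report, voluntary response and gender balance, but not this.

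**Working it through.** **Step 1: the rules side by side.** The only planning figure for this group is the target of 1000 (400,000 births × 1% × 25%). The point does not depend on it. Each combination of exclusions, for a person who meets an inclusion criterion, gives:

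| Exclusions met | Result under the written rule |
|---|---|
| none | included |
| 1 only | included |
| 2 only | included |
| 3 only | excluded |
| 1 and 2 | not defined (the rule speaks of only 1 or 2) |
| 3 with 1 and/or 2 | not defined by the wording, but confirmation is required for entry anyway |

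Exclusion 1 alone therefore never excludes under the combining rule. If exclusion 1 is applied as listed, no changers remain and the section 2.7 comparison cannot be estimated. A woman who was vegan in one pregnancy but changed in another meets inclusion 1 and exclusion 1 together.

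**Step 2: which changers enter under the combining rule.** They need another route: a vegan diet in another pregnancy, a vegan-fed child, or breastfeeding as a vegan. On a lenient reading of inclusion 1, a change partway through a pregnancy may also qualify. Changers without any route are absent.

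**Step 3: illustration of size.** The documents give no rates, so these inputs are assumptions: 50% of vegans meet critical advice; 40% of those and 20% of the others change diet; all non-changers are eligible. Let s1 and s0 be the shares of criticised and uncriticised changers who qualify.

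- Criticised changers A = 0.5 × 0.4 × s1 = 0.20·s1
- Criticised non-changers B = 0.5 × 0.6 = 0.30
- Uncriticised changers C = 0.5 × 0.2 × s0 = 0.10·s0
- Uncriticised non-changers D = 0.5 × 0.8 = 0.40
- Total T = A + B + C + D
- Change rate = (A + C)/T; share criticised = (A + B)/T; odds ratio = A·D/(B·C)

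| s1, s0 | A, C | T | Change rate | Share criticised | Odds ratio |
|---|---|---|---|---|---|
| 1, 1 (truth) | 0.20, 0.10 | 1.00 | 30.0% | 50.0% | 2.67 |
| 0.3, 0.3 | 0.06, 0.03 | 0.79 | 11.4% | 45.6% | 2.67 |
| 0.2, 0.4 | 0.04, 0.04 | 0.78 | 10.3% | 43.6% | 1.33 |
| 0.1, 0.5 | 0.02, 0.05 | 0.77 | 9.1% | 41.6% | 0.53 |
| 0, 0 (exclusion 1 applied) | 0, 0 | 0.70 | 0% | 42.9% | not estimable |

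When s1 = s0 the factor cancels from A·D/(B·C), so the odds ratio is unchanged while the frequencies fall.

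**Step 4: a second set of assumed inputs.** Take change rates of 40% and 10%, with 20% of changers entering whatever advice they had. Then T = 0.5 × (0.6 + 0.08) + 0.5 × (0.9 + 0.02) = 0.34 + 0.46 = 0.80.

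- Change rate: 25% becomes 0.05/0.80 = 6.25%.
- Share criticised: 50% becomes 0.34/0.80 = 42.5%.
- Risk difference: 30 points becomes 0.08/0.68 − 0.02/0.92 = 9.6 points.
- Odds ratio: (0.4/0.6)/(0.1/0.9) = 6.0 before, and (0.08/0.60)/(0.02/0.90) = 6.0 after.

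**The case against.** The strongest reply is that section 2.4 settles itself. The sentence after the list is the operative test, it admits changers, and the section 2.7 comparison fits it; what remains is loose drafting. That is a fair guess at the intention, but the text still labels changers as excluded and leaves people meeting both exclusions undefined. Nor can exclusion 1 be read simply as removing the pregnancy questions: that kind of limit is written only for exclusion 2, and applied here it could remove the answers that section 2.7 needs. The questionnaire is in a supplement not shown. It may reveal which rule was applied, but it would not reconcile the article.

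Several other replies stand in part:

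- Inclusion 1 does not say the whole pregnancy, so more changers may enter than a strict reading allows. This reduces the selection but does not remove it.
- The comparison is only listed as possible, is conditional on enough data, and has descriptive p-values.
- Section 2.6.1 disclaims representativeness and section 5.2 says only respondents' views are captured. Neither tells the reader that eligibility itself removes people who gave up the diet.
- Section 2.7 plans logistic regression for yes/no outcomes, and the odds ratio survives equal retention. This is correct, and it limits the point to frequencies and risk differences unless retention is unequal.

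**Conclusion.** The contradiction is in the text and needs no assumptions. The understatement of how often the diet is changed, and of how often its causes are reported, follows from the entry requirement provided that some changers have no other route in and that the influence makes change more likely. Its size is unknown. The illustrations show a 30% change rate appearing as 9% to 11%, and a 25% rate as 6.25%, all on assumed inputs.

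A reader might infer more than the documents support:

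- **That the study screens on its primary outcome and its influences cannot be interpreted.** Maintenance of the diet is a secondary outcome in section 3.2. Much of the primary content (supplement decisions, information sources, expert opinion) does not rest on the changer comparison. The exact statement is that entry is selected on the behaviour named in one primary objective.
- **That associations are necessarily biased.** This requires entry of changers to differ by the influence studied. Section 2.6.1 links such influences to changing diet, not to which changers later qualify. Unequal entry is plausible, but neither its presence nor its direction is established.
- **That children still under five are barred**, from "do not feed/have never fed their children a vegan diet at least up to the age of 5 years". The inclusion criterion uses the present tense as well as the past, and the article consistently means children up to five. This is awkward wording, not a restriction.

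**What to change.** 1. In section 2.4, remove exclusions 1 and 2 as reasons to exclude a participant. Alternatively, restate them as limits on which question blocks are analysed, keeping the change-of-diet items. Define the status of someone who meets both.
2. In section 2.7, use the pregnancy-level answers to state which changers the comparison covers, for example those who changed in one pregnancy and kept the diet in another, or who changed and later fed a child vegan.
3. In section 2.1.1, restate the objective as influences reported by people who kept the diet in at least one pregnancy or for at least one child.
4. Report the frequency of change and the changed-versus-unchanged comparison as applying only to that selected group.
5. Add this selection to the limitations in section 5.2.

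The cost is rewording, a coding rule for changers, and a narrower conclusion. Widening entry to people who gave up the diet is not proposed: it would define a different population from the one in section 2.6.1, and recruitment was scheduled to end in July 2025.

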## 2. Materials and Methods

### 2.1. Objective

The aim of the descriptive, cross-sectional VedieS study is to investigate, for the first time, the factors influencing vegan parents and pregnant women in adhering to a strictly plant-based diet and in their use of DS, as well as the potential implications for their health and the health of their children up to five years of age. External factors that lead to and influence the development of individual food and nutritional health literacy and the use of DS by vegans are the main research questions. Hence, this approach focuses on the relevant information sources for vegans as the main cause of their food and nutritional health literacy. Not only vegans themselves but also medical experts (pediatricians, gynecologists, general practitioners, pharmacists, dietitians) are being asked about their opinion, knowledge and advice on a vegan diet, to be able to draw conclusions about the quality of information they provide to vegan parents and pregnant women.

Influential factors, sources of information gathering, reasons to choose certain DS, difficulties in administering DS to vegan-fed children (up to the age of 5 years), as well as details about the compliance of DS intake of vegan pregnant women and parents, should be revealed. The results can serve as a starting point for comprehensive information provision for vegans and provide insight into their food and nutritional health literacy. The opinion of medical experts has a decisive influence on the health of vegans. For this reason, the content of their advice will also be assessed as the advisory role of the medical experts is essential to provide vegans with reliable information on a balanced vegan diet and use of DS.

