##### Planned Sample Size for Vegan Participants

The study targets a small and hard-to-reach group whose exact size and characteristics are difficult to determine: individuals who follow a vegan diet during pregnancy or while raising their children. Although estimates suggest that 0.5–1% of the Austrian population follows a vegan diet [51], there are no official data on how many continue this diet throughout pregnancy and early parenthood. It is assumed that some individuals who usually follow a vegan diet may change their diet during these life stages, often due to concerns about nutrient adequacy, limited medical counseling, or external pressures. While exact numbers are unavailable, studies suggest that such factors may lead some vegans to modify or discontinue their diet in pregnancy or because of their children [33,52]. This uncertainty makes it particularly difficult to determine the actual size of the relevant study population. According to national birth statistics, around 400,000 children are expected to be born in Austria over a five-year period [53]. If 0.5–1% of those children are raised in vegan households, this would correspond to an estimated 2000–4000 families. The study aims to reach approximately 25% of this estimated population, resulting in a target sample of 1000 vegan participants. This sample size allows for meaningful descriptive analyses and subgroup comparisons (e.g., supplement users vs. non-users), without implying statistical representativeness.

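### Inclusion 2 and exclusion 2 for vegans word age 5 as a minimum length of vegan feeding, while the objectives use it as an upper age limit, so the population behind the child data is not clearly defined

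*Protocol article*

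**What the plan says.** In section 2.4 (Eligibility Criteria), inclusion 2 for vegans admits parents who feed or fed at least one child "a vegan diet at least between the ages of 0 and 5 years". Exclusion 2 covers "Parents who do not feed/have never fed their children a vegan diet at least up to the age of 5 years", with a qualification in parentheses: "if vegan mothers followed a vegan diet during their pregnancy, exclusion only relates to questions concerning their children".

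Three other provisions of section 2.4 bear on this:

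- Inclusion 3, for vegan mothers or gender-diverse participants who breastfeed or breastfed, adds: "Answering questions regarding their infant(s)/child(ren) up to the age of 5 years will be included".
- The combination rule is that "at least one inclusion criterion (plus participant information) must be fulfilled".
- The closing rule on exclusions is: "If only 1 or 2 is fulfilled, and 3 is not, participants will be included in the survey". Exclusion 3 is failure to confirm the participant information.

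Elsewhere age 5 is a ceiling. Section 2.1 speaks of "the health of their children up to five years of age", and sections 2.1.1, 2.1.2 and 2.2 use the age in the same way. The planning estimate for vegan participants (section 2.6.1) starts from the statement that "around 400,000 children are expected to be born in Austria over a five-year period".

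**The concern.** The words *at least* in both criteria change an age ceiling into a required length of vegan feeding. Two readings result, and they define different populations. On the literal reading, the child must have been fed vegan from birth to age 5. On the inclusive reading, any vegan feeding within that age range is enough, even a few weeks.

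The choice matters for the child outcomes. Supplement administration to children is among the primary outcomes (section 3.1). Compliance and difficulties with dosage forms are secondary (sections 2.1.2 and 3.2). Section 2.7 lists supplement users versus non-users, including for children, as a comparison. The introduction hypothesises that critical or unclear advice may lead families to change diet or avoid supplements. If child answers count only when vegan feeding continued to age 5, the child data are selected on a behaviour under study. For these mothers, reports on a child now in infancy would give way to recall of infancy by those who kept the diet going.

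**Working it through.** **1. The planning figure.** Inputs from section 2.6.1: 400,000 births over five years, a vegan share of 0.5–1%, and a target fraction of about 25%.

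- 400,000 × 0.005 = 2000 and 400,000 × 0.01 = 4000, as stated.
- 0.25 × 4000 = 1000, the stated target. At the lower end 0.25 × 2000 = 500, so the target reproduces only from the upper end of the range. That is a separate matter.

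**2. Fit between that figure and inclusion 2.** At the end of a five-year birth period, no child born within it has completed five years of vegan feeding. On the literal reading, 0 of the 2000–4000 families then meet inclusion 2 through those children. On the upper-limit reading, all of them fall within the age range and the target of 1000 is unaffected. The planning estimate therefore fits only the upper-limit reading.

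**3. The criteria applied literally to a family with a vegan-fed two-year-old.**

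| Respondent | Entry to the survey | Child answers |
|---|---|---|
| Strictly vegan father | Inclusion 1 and 3 do not apply to him; inclusion 2 fails because the child is not yet 5; inclusion 4 opens with parents who make rare exceptions | No clear route |
| Father allowing one exception a month | Inclusion 4 | No minimum child age in inclusion 4 |
| Mother vegan in pregnancy, did not breastfeed | Inclusion 1 | Dropped by the parenthesis in exclusion 2 |
| Mother vegan in pregnancy, breastfed | Inclusions 1 and 3 | Kept by inclusion 3, dropped by exclusion 2 |

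The first two rows show an oddity: the stricter family has the less certain route. The last sentence of inclusion 4 caps exceptions at two a month, and zero satisfies that cap, so one could argue the strict father in. The opening of the same criterion points the other way.

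**4. Whether the closing rule repairs this.** It says that meeting only exclusion 1 or 2 does not prevent inclusion in the survey. It does not waive the requirement for at least one inclusion criterion, so the first row stays unresolved. It governs entry to the survey and says nothing about which answers count, so it does not restore the child answers in the third row or settle the conflict in the fourth.

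**The case against.** The strongest reply is that section 2.4 already limits the damage. One inclusion criterion is enough; inclusions 1, 3 and 4 set no minimum child age; and exclusion 2 alone bars nobody from the survey. Inclusion 3 expressly keeps child answers from breastfeeding vegan mothers. The criteria are written in both present and past tense, which suits parents still feeding a child within the age range. *At least* may only mean that the years 0 to 5 matter and later years do not. On that view this is clumsy wording with an obvious intended meaning.

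Much of this stands. A reader might infer that the criteria remove parents of infants and toddlers altogether and leave only families who lasted to age 5. The documents do not support that, for the reasons just given. Nor do they support sizing the loss from the share of the planned birth cohort who turn 5 during recruitment. The article does not align the five-year birth period with the recruitment dates, section 2.2 opens the survey beyond Austria, and the past tense admits parents of children now older than 5.

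It is also true that the operative screen cannot be seen. Section 2.3 says questionnaire items decide eligibility, and the questionnaires are in a supplement that is not shown. The literal reading may never have been applied.

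What the reply does not answer is the unclear position of strictly vegan non-birth, non-breastfeeding parents, the loss of child answers under the parenthesis, and its conflict with inclusion 3. An intended meaning that must be guessed does not define an analysis set.

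**Conclusion.** The point holds as a contradiction within the stated eligibility rules. Inclusion 2 and exclusion 2 disagree with the objectives, the design, the planning estimate and inclusion 3. Followed literally, they have three consequences:

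- **Entry:** strictly vegan fathers and other non-birth, non-breastfeeding parents of under-fives meet none of inclusions 1–3 and have no clear way in.
- **Child data:** answers from mothers vegan in pregnancy are dropped when the child has not been fed vegan to age 5, so the child outcomes are selected on continued vegan feeding.
- **Consistency:** for breastfeeding mothers in that position, one rule keeps the child answers and another drops them.

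The size cannot be given as a number of participants, because the article states no expected split by parent type, breastfeeding or child age. The only exact figure is the zero overlap between the literal rule and the planning families at the end of the birth period. It shows inconsistency and is not an estimate of lost sample. The actual effect depends on how the unseen screening items were worded. The child population should be settled before analysis in either case.

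**What to change.** Reword inclusion 2 to: *fed at least one child a vegan diet at any time between birth and the fifth birthday*. Reword exclusion 2 to: *never fed a child a vegan diet before the fifth birthday*. Reconcile both with inclusion 3 and the closing rule, stating separately who may enter the survey and whose child answers are analysed. If the sponsor means age 5 to include the sixth year of life, the boundary should say so in every place.

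Use the same definition for the child analysis set, and report child outcomes by child age and by duration of vegan feeding, so that early stoppers and long-term adherers can be told apart. Section 3.2 already lists duration of adherence as an outcome.

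Check the screening items against the new wording. If they used the inclusive reading, the change is two sentences of text and one analysis-set rule. If they screened on the literal wording, a filter cannot recover the child answers or respondents lost, and this should be reported as a limitation. The one small downside is a child set more mixed in feeding duration, which the breakdown addresses.
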